
“One study, one primary outcome”, a novel methodology for clinical trial design, was published by China Food and Drug Administration (CFDA). The core of this concept lies in the supposition that study results will be more credible if the whole study is single-mindedly and exclusively designed for the unique outcome of main interest. Moreover, the SPIRIT guidance suggests a minimum number of primary outcomes in clinical trials because multiple primary outcomes can introduce problems with multiplicity, selective reporting, and interpretation when there are inconsistent results across outcomes [22]. Thus, although this design has not been widely implemented in clinical trials, we prefer to conduct a tentative trial in an attempt to provide some practical information.

The objective of this trial is to demonstrate the superior efficacy and safe of QFGKG over placebo in adult individuals with PIC by addressing the following hypotheses: (1) That QFGKG will significantly shorten the cough duration in patients with PIC; (2) That QFGKG will significantly relieve the main clinical symptoms in patients with PIC; (3) That QFGKG will increase the quality of life in patients with PIC; (4) That QFGKG is safe and will not result in any serious side effects; (5) That the novel design methodology of “one study, one primary outcome” is feasible and desirable in clinical trials.

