### Study participants

A total of 480 patients will be recruited and averagely assigned to each part. Each center will recruit an equal number of patients; 60 patients will be recruited at each individual center in part A and 80 patients will be enrolled at each individual center in part B. Patients, who are diagnosed as having PIC in one of the participating centers according to the guideline issued by the Chinese Medical Association [25], aged between 18 and 65 years, with a TCM syndrome being differentiated as “pathogenic-wind invading lung” based on the Guidelines for Clinical Research of New Chinese Medicine [26], are eligible for enrollment. Diagnosis criteria of PIC are presented in Table 3. Inclusion and exclusion criteria are listed in Table 4, and TCM syndrome diagnostic criteria, based on State Administration of Traditional Chinese Medicine guidelines [27], are elaborated in Table 5. Some discrepancies should be noticed in the inclusion criteria of two parts. Part A is designed to focus on the time when cough can be resolved completely, thus patients’ cough severity is relatively mild in order to yield more expected results. On the other hand, part B is designed to calculate the dynamic change in cough symptom score across four time-points (see Table 2), so the cough severity of patients recruited in this part is relatively severe for more obvious changes.

**Table 3 Tab3:** Diagnosis criteria for postinfectious cough

● Cough that has been present following symptoms of an upper respiratory tract infection;
● Irritable dry cough or cough with small amounts of white mucus;
● Cough lasts for at least 3 weeks, but normally no longer than 8 weeks;
● Negative findings of chest radiograph;
● Negative results of bronchial provocation test and dilation test;
● Exclude other causes which could result in cough, such as upper airway cough syndrome(UACS), cough variant asthma(CVA), eosinophilic bronchitis(EB) and gastroesohageal reflux disease(GERC);
● Exclude severe pulmonary diseases including chronic obstructive pulmonary disease(COPD),lung cancer, pulmonary tuberculosis, et al.;
● Exclude hypertension that involves use of angiotensin converting enzyme inhibitor(ACEI) currently.

**Table 4 Tab4:** Selection criteria for eligible patients

● Inclusion criteria for study part A	● Inclusion criteria for study part B
● Postinfectious cough	● Postinfectious cough
● Syndrome of “pathogenic-wind invading lung”	● Syndrome of “pathogenic-wind invading lung”

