### Interventions

After enrollment, eligible patients will be randomly assigned to receive twice daily QFGKG 12.0 g or twice daily dummy QFGKG (placebo) 12.0 g. The use of placebo as a comparator in this trial largely depends on empirical evidence [17, 28, 29] and Guidelines for Clinical Research of New Chinese Medicine [26]. Besides, the absence of generally recognized therapy and self-healing tendency of PIC also support the use of placebo. QFGKG and placebo in this trial are manufactured by Baotou TCM Co., Ltd. The Latin names, English names and Chinese Pinyin of the four herbs used in QFGKG are listed in Table 6. Both within-group changes and between-group changes are assessed across three time-points during treatment. As to the treatment duration, a longer (14 days) treatment in part A is conducted for the sake of more cured cases, while a shorter treatment (10 days) in part B is enough for monitoring noticeable changes in cough symptom score. A two-day follow-up will be conducted for all patients. At the initial drug dispensing stage, patients are advised to strictly follow protocol instructions, which will be reiterated at each study visit. Participants are requested to genuinely report their daily dosage of drugs that have been actually taken and to return unused ones to physicians at each study visit. Drug using and returning will be recorded on CRF by physicians. Unused drugs will be finally collected and counted by drug managers and then be destroyed by the sponsor at the end of the trial. All previous and concomitant treatments, including drug and non-drug therapies, taken one week before and during the intervention will be recorded on CRF. Concomitant treatment for comorbidities such as hypertension, diabetes and other chronic conditions are permitted during the intervention. Whereas, the use of antibiotics, Western or other antitussives, and non-drug cough suppressing therapies such as acupuncture and cupping are strongly discouraged to prevent potential systemic effects. Participating centers are required to record dropout cases and reasons, and also side effects happen during the intervention.

**Table 6 Tab6:** Latin name, English name and Chinese pinyin of the four herbs

Latin name	English name	Chinese pinyin
*Ephedra sinica Stapf*	Herba Ephedrae	Ma Huang
*Sinomenium acutum*	Caulis Sinomenii	Qing Feng Teng
*Stemona japonica (Blume) Miq.*	Radix Stemonae	Bai Bu
*Aster tataricus L.f.*	Aster tataricus	Zi Wan

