#### Part B

##### Primary outcome

The primary outcome of part B is cough symptom score, which will be assessed across baseline, 6 ± 1 days into the intervention, post-intervention (11 ± 1 days) and 2 days post-intervention if necessary. Simplified cough symptom score (SCSS) recommended by Chinese Medical Association [30] is developed based on the Asthma and Cough Symptom Score Estimation Method [31]. It consists of daytime score and nighttime score, ranging from 0 to 3, respectively. The cough symptom score scale is provided in Table 7. SCSS, which is usually used to determine the frequency and diurnal variation of cough, and also to reflect the quality of life, has been verified as reproducible and well-responsive to treatments [32]. Daytime is arbitrarily defined as 8 a.m. to 8 p.m. and nighttime as 8 p.m. to 8 a.m.

**Table 7 Tab7:** Cough symptom score scale

Score	Daytime cough symptom score	Nighttime cough symptom score
0	no cough during the day	no cough during the night
1	occasional cough for short periods	cough for short periods before sleep or occasional cough during the night
2	frequent coughing, which did slightly interfere with usual daytime activities	frequent coughing, which did slightly interfere with sleep
3	distressing coughs, which did seriously interfere with usual daytime activities	distressing coughs preventing any sleep

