### Statistical analysis

Beijing Qihuang Medicine Clinical Research Center is in charge of data statistical analysis. The statistical analysis will be masked. A group of professional statisticians who are independent of all the other process of the study would perform the statistical analysis. Full Analysis Set (FAS) would be applied for all participants who have been randomly allocated and have taken QFGKG or placebo. Non-completers who never use any test drugs will be excluded. Missing values of primary variations will be imputed using the last observation carried forward (LOCF) approach according to intention-to-treat (ITT) principle. Cases in Per Protocol Set (PPS) are those who thoroughly adhere to the protocol without absence of baseline characteristics. Analysis of primary outcome and curative effect will be carried out using FAS approach and PPS approach. Safety Analysis Set (SS) includes all randomized patients who have accomplished at least one study visit. Participating centers are required to sum up participants number in each set and list participants who are removed from PPS. The Chi-square test or Fisher’s exact test will be performed for the categorical variables, and the Student’s t-test will be used for continuous normally distributed variables. For data that is not normally distributed, intra-group or inter-group differences before and after treatment will be analyzed by Wilcoxon rank sum test. The proportion of patients with adverse events in two groups will be compared using the chi-square test or Fisher’s exact test. The statistical significance level is set at *P* < 0.05 and relative risk (RR) with corresponding 95 % confidence interval (CI) to compare dichotomous variables will be calculated. Table 8 shows the method of analysis for specific outcomes.

**Table 8 Tab8:** Outcomes and methods of analysis

Outcome/variable	Hypothesis	Measures	Methods of analysis
Baseline balance test		Quantitative outcomes (age, disease duration, body temperature, heart/respiratory rate, blood pressure)	T-test/Wilcoxon rank sum test
		Qualitative outcomes (gender, marriage, race, previous treatment)	Chi-squared test/Fisher exact test/rank-sum test
Adherence at post-intervention		Percent and cases of adherence in previous 10/14 days < 80 %, > 120 % and 80 %-120 %	Chi-squared test/Fisher exact test
Concomitant treatments		Percent and cases of concomitant treatments	Chi-squared test/Fisher exact test

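### The protocol assigns an unpaired rank-sum test to paired within-arm changes, and part B's primary cough score has no named deciding visit and a follow-up assessment of contradictory status

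*Protocol article*

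**What the plan says.** **Test for non-normal data.** The Statistical analysis section of the protocol article states that "intra-group or inter-group differences before and after treatment will be analyzed by Wilcoxon rank sum test". The sentence is a general rule for the trial and is not tied to one outcome.

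**Part B's primary outcome.** Under Outcome measures, "The primary outcome of part B is cough symptom score, which will be assessed across baseline" and then at day 6 ± 1, "post-intervention (11 ± 1 days) and 2 days post-intervention if necessary". The Study participants section adds that "part B is designed to calculate the dynamic change in cough symptom score across four time-points". Table 8 offers a t-test or a rank-sum test for this score, with no covariate, and its Measures cell is empty. No section says which visit decides.

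**Within and between arms.** Interventions states: "Both within-group changes and between-group changes are assessed across three time-points during treatment".

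**The follow-up score.** Interventions also states: "A two-day follow-up will be conducted for all patients". Table 2 marks the cough symptom score at Visit 3 with no condition attached.

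**Reason for the design.** The Background defends one primary outcome per study part partly because "multiple primary outcomes can introduce problems with multiplicity, selective reporting, and interpretation".

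**The concern.** There are three separate defects.

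1. The rank-sum test assumes independent samples. Two scores from the same patient are not independent, so the test uses the wrong variance for a within-arm change. The non-normal branch is the likely one for this outcome. The total is the sum of two items scored 0 to 3, and part B requires a total of at least 4, so baseline can only be 4, 5 or 6.

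2. A primary outcome followed over several visits, with no visit named, leaves room to choose the visit after the results are seen. The trial was split into two parts to avoid that kind of selection between outcomes, so it should not be left open between visits.

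3. If sites follow the outcome section, follow-up scores will exist only where someone judged them necessary, a subset selected after randomisation. The Statistical analysis section carries the last observation forward for missing primary values, so an untaken follow-up score could be filled with the Visit 2 value. A later analysis plan cannot recover scores that were never collected.

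**Working it through.** The article gives no figure of its own to reproduce on this point, and no standard deviation or correlation for the cough score. The correlations below are therefore assumptions, shown as ranges.

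**A. Rank-sum test on paired data**

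Inputs: 180 QFGKG and 60 placebo patients per part (Abstract); correlation ρ between a patient's two scores of 0.3, 0.5 or 0.7 (assumed).

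An unpaired comparison takes the variance of the mean difference as 2σ²/n, whereas for paired scores it is 2σ²(1 − ρ)/n. For normal scores, the true size of a nominal two-sided 5% unpaired test is about 2[1 − Φ(1.96/√(1 − ρ))]:

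- ρ = 0.3: 1.96/0.837 = 2.34, size about 0.019
- ρ = 0.5: 1.96/0.707 = 2.77, size about 0.006
- ρ = 0.7: 1.96/0.548 = 3.58, size about 0.0003

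Simulation of the rank tests themselves (2,000 runs, normal scores; power is for a 0.3 SD within-arm change):

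| ρ | n | Size, rank-sum | Size, signed-rank | Power, rank-sum | Power, signed-rank |
|---|---|---|---|---|---|
| 0.3 | 60 | 0.029 | 0.056 | 35% | 48% |
| 0.5 | 60 | 0.009 | 0.049 | 30% | 59% |
| 0.7 | 60 | 0.001 | 0.055 | 28% | 82% |
| 0.3 | 180 | 0.017 | 0.045 | 83% | 91% |
| 0.5 | 180 | 0.006 | 0.042 | 87% | 97% |
| 0.7 | 180 | 0.0005 | 0.050 | 92% | 99.8% |

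The simulation used continuous scores and did not model the many ties of a 0-to-6 scale. The direction is clear: the unpaired test rejects too rarely and loses power.

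The paired test does not make within-arm p-values informative about the drug. With no drug effect, a natural improvement of 0.25 or 0.5 SD (assumed, ρ = 0.5) makes the 180-patient QFGKG arm significant in 70% or 100% of runs, even with the rank-sum test.

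**B. What an unnamed visit could cost**

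There are two post-baseline scores (Visits 1 and 2), or three with the follow-up visit. Suppose a between-arm p < 0.05 at any of them counted as success.

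- Independent visits: 1 − 0.95² = 0.0975 for two; 1 − 0.95³ = 0.1426 for three.
- Equally correlated visits (1,000,000 draws of normal test statistics):

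| Between-visit correlation (assumed) | Two visits | Three visits |
|---|---|---|
| 0.5 | 0.091 | 0.126 |
| 0.7 | 0.083 | 0.109 |

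One test at one named visit stays at 0.05.

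**C. What adjustment for baseline could gain**

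With correlation ρ between baseline and Visit 2, and relative to an unadjusted comparison of Visit 2 scores, the variance of the between-arm difference is multiplied by 2(1 − ρ) for a change score and by 1 − ρ² for ANCOVA.

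- ρ = 0.3: 1.40 and 0.91
- ρ = 0.5: 1.00 and 0.75
- ρ = 0.7: 0.60 and 0.51

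ANCOVA is never the worse of the two. Because entry restricts baseline to three values, the lower correlations may be nearer the truth, and the gain correspondingly modest.

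**D. The follow-up score, side by side**

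- Outcome measures, Part B: taken "2 days post-intervention if necessary".
- Interventions: "A two-day follow-up will be conducted for all patients".
- Table 2: cough symptom score marked at Visit 3, unconditional.

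The first statement cannot stand with the other two.

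**The case against.** The strongest reply is that this is a condensed article whose analysis plan is not shown, and that the deciding visit, contrast and covariates are commonly set there. That stands in part: the unnamed visit alone would be a request for clarification. It does not cover the paired-data error or the follow-up conflict, which are stated in the text.

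The rank-sum error also has a limited reach. It does not touch the between-arm comparison, and it makes within-arm tests conservative, so it creates no false-positive risk for the superiority claim. That is right.

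Three stronger readings are tempting, and the document does not support them.

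- *Part B's primary analysis is fixed as within-arm comparisons.* The sentences in Interventions and Statistical analysis are general. Table 8 uses the same method label for baseline balance and intervention duration, which are comparisons between arms.
- *The article contradicts itself on three versus four time-points.* Interventions counts three during treatment (baseline, Visits 1 and 2). Study participants refers to Table 2, which adds the follow-up visit. The two counts agree.
- *Table 8's hypothesis wording lets within-arm improvement count as success.* The same wording fills every efficacy row, including the log-rank rows, while the Background and Study designs sections both state superiority over placebo.

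Finally, the Background's multiplicity remark is about multiple outcomes, and the design claims one primary outcome, not one primary test. Repeated visits raise a similar problem, but the article does not break a promise it made.

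**Conclusion.** The point holds in a limited form. The test named for within-arm differences is wrong for paired data. Its effect is conservative, with true size of about 0.05% to 3% at assumed correlations of 0.3 to 0.7, and it is confined to comparisons that cannot establish superiority. The status of part B's follow-up score is contradictory and affects which data are collected. The primary comparison is given only as an unadjusted two-sample test with no deciding visit.

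The error rates of 8–9% for two visits and 11–13% for three are conditional on a rule that any visit may win, and on assumed correlations of 0.5 to 0.7. They are not this trial's error rate, because the article neither adopts nor excludes such a rule. They show what naming one visit would rule out.

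**What to change.** 1. Make part B's primary test one between-arm comparison of total cough symptom score at Visit 2 (day 11 ± 1), adjusted for baseline score and centre, for example by ANCOVA. Baseline is already collected and centre is already a stratification factor. ANCOVA is one suitable choice for a 0-to-6 total, not the only one.
2. Make the other visits secondary.
3. Report within-arm changes descriptively. If a p-value is kept, use a paired method such as the signed-rank test, and keep the rank-sum test for between-arm comparisons.
4. Reconcile Interventions, the Part B outcome section and Table 2 on whether the follow-up score is taken in all patients, and tell the sites.

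The cost is wording in the protocol or analysis plan. The article reports recruitment still in progress (318 included), so the change could be made before unblinding. The small downside is that other visits can no longer carry the primary claim.

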### Randomization and blinding

Eligible patients will be randomized in a ratio of 3:1 to QFGKG group or placebo group, with stratification by participating center. A centralized randomization will be employed. The random coding of each center as well as the allocation sequence are generated electronically using SAS 6.12 software. Assignments are concealed in sequentially prepared coded, sealed, opaque envelopes, in which the corresponding intervention group of the randomization list will be found. A professional statistician who is independent of intervention and data collection is appointed to choose appropriate block length to ensure concealment. A group of research assistants who are not involved in recruitment, intervention or assessment of outcomes will prepare the envelopes. Staff responsible for recruitment is not allowed to take part in the group allocation. Only after the former participant is enrolled and his/her baseline testing is completed, the next envelope could be opened by researchers responsible for allocation. Participants will be randomized to the intervention group or the control group in line with numbered envelope under instructions from drug managers at each center. Blind codes along with random seeds and block length will be recorded in duplicate and delivered to Good Clinical Practice (GCP) Centre of West China Hospital and the sponsor for safekeeping. Patients and all engaged personnel including the sponsor remain blind to allocation and intervention throughout the whole process. Placebo will be packaged with imitative similarity in appearance, smell and taste with QFGKG. However, personnel who are designated to prepare drug packaging and labeling will not be blinded. The prepared emergency code-break envelope that contains allocation information, and emergency measures as well as contact details of the responsible department will be distributed to study centers along with drugs. Patients reported side effects will be recorded in the case report forms (CRFs) detailedly by physicians at visit 1 and visit 2. If an unpredictable severe adverse event happens, the chief investigator is qualified to open the emergency envelope and guide physicians to treat the patient according to emergency measures. The patient must be withdrawn and be followed up until he/she recuperates. In this case, the chief investigator should report the case to hospital ethical committee and drug administration agency. The broken code and reasons for unblinding should be recorded on CRF. Meanwhile, severe adverse event report form (SAERF) will also be completed. During the revealing, allocation information must not be disclosed to the patient and any third party.

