
### Sample size

The latest edition of Provisions for Drug Registration issued by CFDA recommends a minimum number of 300 for subjects enrolled in the trial group in a phase III clinical trial. Sample size calculation of this trial results in 24 patients in total for part A (18 in the QFGKG group and 6 in the placebo group) and 56 patients in total for part B (42 in the QFGKG group and 14 in the placebo group), respectively. Obviously, the calculated patient number in the QFGKG group is much smaller than the recommended one. Given the above, we set the sample size according to the Provisions for Drug Registration. 480 patients in total would be included, with 360 being assigned to the QFGKG group and 120 being assigned to the placebo group, considering a maximal dropout rate of 20 %. Calculation assumed an 80 % power for a two-sided log-rank test at a 5 % significance level.

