Intervention duration		Formula: the last day using test drugs-the first day using test drugs + 1	T-test/Wilcoxon rank sum test
Primary			
Time to cough resolution	improvement occurred		Kaplan-Meier method/Log-rank test
Cough symptom score	improvement occurred		T-test/Wilcoxon rank sum test
Secondary			
VAS score	improvement occurred		T-test/Wilcoxon rank sum test
TCM symptom score	improvement occurred		T-test/Wilcoxon rank sum test
TCM curative effect	improvement occurred	Percent and cases of four grades: complete recovery, excellent effect, modest effect and no effect	Cochran-Mantel-Haenszel Chi-squared test
CQLQ score	improvement occurred	Questionnaire	T-test/Wilcoxon rank sum test
Cough disappearance rate	improvement occurred		CMH Chi-squared test
Time to cough relief	improvement occurred		Kaplan-Meier method/Log-rank test

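### Table 8 gives neither primary test a centre stratum or a baseline covariate: both are valid, but conservative and less precise to the extent that centre or baseline predicts outcome

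*Protocol article*

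**What the plan says.** Under Randomization and blinding: "Eligible patients will be randomized in a ratio of 3:1 to QFGKG group or placebo group, with stratification by participating center". Study designs says the same, adds that allocation is in blocks, and lists six centres defined mainly by geography.

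The cough symptom score is marked at baseline in Tables 1 and 2, so every patient in both parts has one.

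Table 8 names a method for each outcome. For time to cough resolution (part A primary) it is "Kaplan-Meier method/Log-rank test". For cough symptom score (part B primary) it is a t-test or Wilcoxon rank sum test; the Statistical analysis text says the "t-test will be used for continuous normally distributed variables", with the rank sum test otherwise. Neither entry mentions centre or a covariate. That text also speaks of comparing before-and-after differences between groups, so the part B comparison may be of change from baseline. The article does not settle this. Cochran-Mantel-Haenszel tests, which can be stratified, are named for two secondary outcomes, without saying by what.

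**The concern.** When randomization is blocked within centres, the arms are balanced on centre by design. An analysis that leaves centre out still counts between-centre variation as noise in the treatment comparison.

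- In part B the t-test standard error is then larger than the true one.
- In part A the mechanism differs: the unstratified log-rank test estimates an attenuated effect and rejects too rarely under the null.

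The baseline score offers a further gain. Part A admits a daytime and/or nighttime score of at least 2, so totals at entry run from 2 to 6, and starting severity plausibly predicts time to a score of zero. Only 60 patients per part receive placebo. The baseline comparisons listed in Table 8 do not include the cough score, so a chance imbalance in it would be neither adjusted for nor, as listed, examined.

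What is at stake is interval width and, if the true effect is modest, power.

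**Working it through.** **Inputs from the article.** "Calculation assumed an 80 % power for a two-sided log-rank test at a 5 % significance level". 240 patients per part, 180:60 (Abstract). Six centres, taken as 40 each. (Study participants gives 60 and 80 per centre, which would total 360 and 480; 240 per part is used here.) Maximal dropout 20%. No hazard ratio, SD, event rate, centre variance or baseline correlation is given, so these are assumed below.

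**1. The plan's own sizes.** "Sample size calculation of this trial results in 24 patients in total for part A", and "56 patients in total for part B (42 in the QFGKG group and 14 in the placebo group"). Without effect sizes these cannot be reproduced, only inverted. Let S = 1.960 + 0.842 = 2.80.

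- Part A (Schoenfeld, 3:1): HR = exp(S/√(0.75 × 0.25 × 24)) = exp(2.80/2.12) = 3.75 if all 24 patients have an event; 4.38 at 80% events; 5.50 at 60%.
- Part B (as two means): d = 2.80 × √(1/14 + 1/42) = 0.865 SD. Read as a log-rank calculation, 56 patients would imply HR 2.37 if all have an event.

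Unadjusted power at the planned size:

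- Part B, 180/60: 0.865/√(1/60 + 1/180) = 5.80; Φ(5.80 − 1.96) = 99.99%. After 20% dropout (144/48): Φ(5.19 − 1.96) = 99.94%.
- Part A at HR 3.75: about 99.9% or more with 192 to 240 patients and 40% to 80% events.
- Effects detectable with 80% power: 0.42 SD (180/60) or 0.47 SD (144/48) in part B; HR about 1.6 to 2.1 in part A.

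**2. Part B, centre.** Let ICC be the share of score variance lying between centres. The true variance of the treatment difference is (1 − ICC) times what the t-test uses. True type I error = 2 × P(Z > 1.96/√(1 − ICC)). Where a centre-adjusted test would have 80% power, the unadjusted test has Φ(2.80 − 1.96/√(1 − ICC)).

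| ICC (assumed) | True type I error | Power |
|---|---|---|
| 0 | 5.0% | 80% |
| 0.05 | 4.4% | 78.5% |
| 0.10 | 3.9% | 76.9% |
| 0.20 | 2.8% | 72.9% |

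**3. Part B, baseline.** Let r be the correlation of baseline with final score. In sample-size terms ANCOVA is worth 1/(1 − r²) against the final-score t-test and, with equal variances, 2(1 − r)/(1 − r²) = 2/(1 + r) against a change-score t-test.

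| r (assumed) | v final score | v change score |
|---|---|---|
| 0.1 | 1.01 | 1.82 |
| 0.3 | 1.10 | 1.54 |
| 0.5 | 1.33 | 1.33 |

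Part B requires a total of at least 4 on a 0 to 6 scale, so baseline can only be 4, 5 or 6. That tends to lower r, and it may make the baseline SD smaller than the final SD. If the baseline SD is k times the final SD, the change-score variance exceeds the ANCOVA variance by (1 + k² − 2rk) − (1 − r²) = (k − r)², in units of the final-score variance. ANCOVA is therefore never worse, but the last column shrinks: for k = 0.5 and r = 0.3 (assumed), 0.95/0.91 = 1.04.

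**4. Part A, centre.** Simulated trials with six centres of 30:10, 14 days, placebo daily resolution 8% and HR 1.6 (all assumed but the design). Power is unstratified v centre-stratified log-rank; simulation error is about 1 point.

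| SD of centre log-hazard | 3,000 trials | 1,200 trials |
|---|---|---|
| 0 | 77 v 77% | 79 v 78% |
| 0.2 | not run | 77 v 77% |
| 0.3 | 74 v 76% | 76 v 79% |
| 0.5 | 68 v 74% | 68 v 75% |
| 0.8 | 55 v 73% | 57 v 75% |

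At SD 0.8 the null rejection rate was 2.5 v 5.2%. A separate run at HR 1.75 (2,000 trials, baseline hazard 0.07 per day) gave 87.0 v 86.4% at SD 0, 84.9 v 86.5% at 0.3 and 76.3 v 83.5% at 0.6. At HR 3.75 both versions rejected in every run at every SD tried.

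For scale, centres at ±2 SD differ in hazard by exp(4 × 0.3) = 3.3-fold, exp(4 × 0.5) = 7.4-fold and exp(4 × 0.8) = 25-fold.

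**The case against.** Four points can be made for the plan.

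- **It is SAP detail.** A condensed article may leave strata and covariates to the SAP, and a bare reference to a log-rank test does not say unstratified. This carries some weight: an SAP could add the stratum without contradicting Table 8. But the article does not defer the method. It names a test for each outcome, so the wording can be judged as it stands.
- **Power was not the constraint.** The size follows a regulation that "recommends a minimum number of 300 for subjects enrolled in the trial group in a phase III clinical trial". At the implied effects, power is near 100% with or without adjustment. This stands, and it limits the point mainly to interval width, plus power if the true effect is far smaller than the one planned for.
- **Centre effects may be small.** With none, stratifying gains nothing; at SD 0.2 to 0.3 it gains 0 to 3 points. The large losses need strong heterogeneity. This also stands.
- **Baseline may be used in part B.** A change score would use it, though less efficiently than ANCOVA.

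A reader might go further and infer that the primary analyses are invalid, or that power has certainly been lost. The documents support neither. Any error in the tests is on the conservative side, and nothing in the article gives the centre variance or baseline correlation needed to show an actual loss.

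**Conclusion.** The point holds as a conditional weakness in efficiency. The named primary tests use neither the randomization stratum nor, as a covariate, a baseline value already collected. If centre or baseline predicts outcome, they are conservative and less precise than they need be. If neither does, adjustment gains nothing, and in the part A simulations without centre effects stratifying cost nothing measurable.

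On assumed inputs:

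- **Part B:** type I error 5.0% to 2.8% for ICC 0 to 0.20. ANCOVA is worth about 1% to 33% more patients than a final-score t-test for r of 0.1 to 0.5, with the lower part of that range more likely given the narrow entry range.
- **Part A at HR 1.6:** essentially no difference in power without centre effects, 0 to 3 points at SD 0.2 to 0.3, about 6 to 7 at 0.5 and about 18 at 0.8.

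Power is a practical issue only if true effects are near 0.4 to 0.5 SD or HR 1.6 to 2.1, well below those implied by the calculated sizes.

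**What to change.** State the following in Table 8, or in the SAP, before unblinding.

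- **Part A:** log-rank test stratified by centre, with the hazard ratio and interval from a Cox model stratified by centre and adjusted for baseline total cough score. Say that this hazard ratio is conditional on centre and baseline.
- **Part B:** ANCOVA of the total cough symptom score at Visit 2 (end of treatment), with baseline score and centre as covariates; a centre-stratified (van Elteren) rank test as sensitivity analysis.

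The cost is wording. Centre and baseline score are already recorded, the analysis is planned to be masked, and recruitment was still under way at publication. The ANCOVA spends six degrees of freedom (five for centre, one for baseline), which is negligible with 240 patients.
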